## Abstract

**Background:**

Venous ulcers usually present a torpid evolution with a negative impact on patients’ quality of life. In primary care, they account for 2.5% of nursing consultations and their treatment represents high costs for national health systems. These patients usually have a low level of physical activity, with muscle pump dysfunction of the lower limbs, which may improve with increased physical activity. The purpose of this study is to analyse the effectiveness of a structured intervention involving physical activity and exercise (Active Legs) as an adjuvant treatment in improving healing of chronic venous ulcers at 3 months follow-up.

**Methods:**

A randomized, multicentre clinical trial. A total of 224 individuals receiving primary nursing care with a diagnosis of venous ulcer, with a diameter of 1 cm or greater and an ankle-brachial index between 0.8 and 1.3, able to comply with the study requirements and consenting to participate, will be sequentially included (112 per group).

Both groups will receive the standard treatment in primary care, with cleansing, debridement and healing in a moist environment together with multilayer compression therapy. The intervention group will also receive a structured educational intervention involving lower limb physical exercise and daily ambulation guidelines.

The primary response variables will be complete healing –understood as complete and sustained epithelialisation for at least 2 weeks– and time to healing. The secondary variables will be degree of healing, ulcer area, quality of life, pain and variables related to the healing process, prognosis, and recurrences. Sociodemographic variables, adherence to treatment and satisfaction variables will also be recorded. Data will be collected at baseline, at 3 months and at 6 months follow-up. Survival analysis (Kaplan-Meier and Cox) will be performed to measure primary effectiveness. Intention-to-treat analysis.

**Discussion:**

If the intervention is effective, a cost-effectiveness analysis could be conducted and implemented as an additional intervention in the usual venous ulcer treatment in primary care.

**Trial registration:**

NCT04039789. [https://ClinicalTrials.gov]. 07/11/2019.

**Supplementary Information:**

The online version contains supplementary material available at 10.1186/s12912-023-01214-y.

## Background

Ulcers of venous aetiology are lesions caused by a process of chronic venous insufficiency [1, 2], with a tendency to a torpid evolution, a low tendency to spontaneous healing [1, 3] and a high recurrence rate [4, 5]. For diagnosis, in addition to the presence of signs of chronic venous insufficiency, it is necessary to assess the ankle brachial index (ABI) [2].

In Spain, lower limb ulcers have a prevalence of 0.1 to 0.3% in the adult population [2] and an incidence of 3 to 5 new cases per thousand people annually (2.6), both values becoming twice as high in the over-65 population segment [2]. Venous ulcers (VU) account for 75–80% of all lower limb ulcers [2, 6] with an average duration of 10.7 months (+ − 27 months) and over 50% being recurrent ulcers [1, 2]. They represent 2.5% of primary care consultations and between 1.5 and 3% of total healthcare expenditure in neighbouring countries [1].

In clinical terms, ulcers of venous origin usually show signs such as high levels of exudate, malodour, moderate pain, and infection, causing sleep disturbances, mobility problems, decreased vitality and even dependence in performing basic activities of daily living [7–9]. A negative emotional impact and a low perceived quality of life have also been observed [10, 11].

There are two main components to ulcer treatment. On the one hand, the topical healing of the wound, favouring a moist environment through the use of dressings [1], and on the other hand, the control of chronic venous insufficiency through the use of compression therapy [1, 12].

Recent studies show that these patients suffer from muscle pump dysfunction of the lower limbs [13, 14], resulting in poorer healing rates [5] and decreased ankle mobility [15, 16] associated with a process of fibrosis involving the Achilles tendon [16].

The lack of competence of the muscle pump, together with the decreased ankle mobility and the age at which VUs are most prevalent (over 65 years) could be among the reasons why approximately 50% of patients suffering from VU have an insufficient level of physical activity (less than 10 min of ambulation per day), as suggested by various authors [5, 7, 13, 17].

In recent years, the published studies have demonstrated the positive effects of the daily practice of an exercise and daily ambulation program at home on the functioning of the calf muscle pump [5, 17, 18], the improvement in ankle mobility [16, 19], the significant increase in tissue perfusion parameters [4, 11, 14] and the improvement of more active lifestyle behaviours among patients [7]. Two systematic reviews published in 2018 with a total of 405 patients recommend the use of aerobic and resistance exercise in the treatment of venous ulcers [20, 21].

With regard to the type of exercises to be performed, there is evidence that a standing position on tiptoe, as well as the flexion-extension of the feet in a seated position, effectively stimulate the calf muscle pump and improve venous return [14, 17, 22]; lower limb resistance exercises also showed benefits in muscle pump functionality and ankle mobility [16, 23] while daily ambulation is also effective as it allows for increased blood pumping from the leg to the heart [11, 14, 17], along with an improvement in the leg muscle pump due to the movement of the ankle joint [5, 14, 16].

Most of the revised studies have been conducted in the United Kingdom, Poland, Brazil, Australia, the Netherlands, and the United States, with small sample sizes. We have not found scientific evidence in Spain on the study of the influence of exercise on the healing of venous ulcers, which justifies the need to conduct this trial, the aim of which is to compare the effectiveness of a structured educational intervention in physical exercise versus the standard practice in the healing of venous ulcers.

## Methods/design

### Main objective

To evaluate the effectiveness of the “Active Legs” intervention as an adjuvant treatment to standard primary care management of venous ulcers for improving the rate of complete healing at 3 months follow-up compared with the usual practice.

### Secondary objectives

To determine whether the Active Legs intervention produces better results than the standard practice on the rate of venous ulcers with complete healing at 6 months follow-up, the degree of healing achieved, the number of recurrences, the quality of life and the pain, as well as to describe the degree of adherence to and satisfaction with the intervention.

#### Design and setting

A pragmatic, randomized, multicentre, open-label, clinical trial of two parallel groups with 6-month follow-ups. The SPIRIT checklist are available as supporting information (see Additional file 1).

#### Setting and study population

The study will be carried out in 16 primary care health centres in the Region of Madrid.

It will include participants aged 18 or older, with a diagnosis of venous ulcer recorded in the electronic medical record (ABI greater than 0.8 and less than 1.3; diameter of the lesion greater than or equal to 1 cm) and under treatment in primary care nursing consultations. The individuals must be able to walk with or without the aid of devices, understand and answer the questionnaires autonomously, be accessible throughout the duration of the study and have expressed their agreement to participate and signed the consent form.

Those who are unable to commute to the health centre, or who reside outside the area where the research is carried out for more than 6 months per year, will be excluded. People with mixed ulcers, deep vein thrombosis (DVT) in acute phase, decompensated heart failure, dermatitis in acute phase, rheumatoid arthritis, undergoing treatment with antineoplastic drugs or with some absolute contraindication for physical exercise will also be excluded.

Withdrawal criteria are set for patients who, during the course of the trial, present a change in their clinical condition that prevents them from further participation, such as inflammation of the locomotor system (with heat, flushing, pain and functional impotence) or trauma due to a fall during the course of program with or without fracture and/or haematoma at both joint and soft tissue level (muscle and tendons) [24], must drop out of the study.

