#### Interventions

The **control group** will receive the usual treatment following the recommendations for the treatment of skin ulcers of the Madrid Health Service [1], which consists of assessment, cleansing, antisepsis, debridement, topical treatment (healing in a moist environment through the use of dressings) and multilayer compression therapy.

The **intervention group** will receive the usual treatment together with the “Active Legs” intervention, which consists of an evidence-based, structured, nurse-led educational intervention in health centre consultations. It incorporates a home-based lower limb exercise program and daily ambulation guidelines. Figure 1 shows schematically the different components of both the control and the Active Legs interventions. The home lower limb exercise program consists of four exercises of progressive difficulty, which the patient will perform twice a day, at least 5 days a week. In addition, patients will be required to follow a program of progressive daily ambulation until the target of 150 min/week (30 minutes for 5 days a week) is reached [25]. The detailed intervention is described using TIDieR (see Additional file 2).

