### Losses in participation

Losses and dropouts during the study and their cause, as well as patients who are required to drop out because of withdrawal criteria, will be recorded. In order to minimise potential losses, as a method of encouraging participation, patients and/or carers will be contacted by telephone to arrange visits.

In the event of dropouts during follow-up, at least 2 telephone calls will be made to record their cause.

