### Analysis

A descriptive analysis (means, medians, frequencies of distribution) will be performed. The results for the primary outcomes will be analysed on an intention-to-treat (ITT) basis. To analyse the principal effectiveness the incidence rates of completely healed ulcers will be compared with their point estimate and 95% confidence interval. Time to complete healing will be compared using Kaplan-Meier curves (Log-rank test). A Cox regression model will be used to adjust for prognostic factors.

To analyse secondary outcomes, an explanatory model will be fitted with linear or logistic analysis, as appropriate.

Significance will be set at *p* < 0.05. All analyses will be performed using STATA software.

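### Patients who meet a withdrawal criterion must leave the study, not only the exercise programme. This causes avoidable loss of the primary outcome, probably mostly in the intervention arm, and undermines the stated ITT analysis.

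*Protocol article*

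**What the plan says.** **The rule.** Setting and study population sets withdrawal criteria for patients who, during the trial, "present a change in their clinical condition that prevents them from further participation". Two examples follow: inflammation of the locomotor system, and "trauma due to a fall during the course of program with or without fracture and/or haematoma at both joint and soft tissue level". The sentence ends by stating that these patients "must drop out of the study".

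**Who has a programme.** Under Interventions, Active Legs is described thus: "It incorporates a home-based lower limb exercise program and daily ambulation guidelines". The control group "will receive the usual treatment following the recommendations for the treatment of skin ulcers of the Madrid Health Service", with no exercise component.

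**What is kept after withdrawal.** Losses in participation says that dropouts and their cause, and also "patients who are required to drop out because of withdrawal criteria, will be recorded". Data collection methods says much the same. Neither section says that wound status is still assessed in these patients.

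**The analysis.** The Analysis section states: "The results for the primary outcomes will be analysed on an intention-to-treat (ITT) basis". The primary outcomes are complete healing at 3 months (yes/no), where closure must hold for two weeks, and time to healing.

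**The concern.** The rule joins two separate events: stopping an assigned activity and ending observation. ITT compares the arms as randomised, whatever happens to treatment afterwards, and so needs each patient's outcome. Here the protocol itself orders observation to end after a post-randomisation event that the assigned treatment can cause.

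Two features make this worse than ordinary dropout. First, the fall example is tied to a programme that controls do not have, so the loss is likely to be unequal between arms. Second, the trial's own rationale (Background) is that mobility and calf-pump function drive healing. A patient with an injured leg may therefore heal differently from those who stay. If so, censoring that patient in the Kaplan-Meier and Cox analyses is not independent of outcome.

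A later analysis plan can choose how to handle the missing results, but it cannot recover wound status that nobody recorded.

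**Working it through.** **Step 1: the passages side by side.**
- *Exit from what?* From the study. The rule does not say that only the exercise stops.
- *Which arm?* The general test and the inflammation example are worded for all participants during the trial. Only the fall example refers to the programme, which only the intervention arm receives. So the loss is mainly, not solely, in that arm.
- *What remains?* The fact of dropout and its cause, with no stated provision for later healing data.
- *What does the analysis need?* Healing at 3 months and time to healing for everyone randomised.

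**Step 2: the plan's own figure.** The plan gives no rate for these withdrawals, only a general 20% allowance for loss. Its 112 per group is 93 × 1.2 = 111.6, rounded up, which leaves 112 − 93 = 19 patients per arm.

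**Step 3: illustration of size.** Inputs:
- True healing P = 50% in both arms, so no effect. The 50% is the 12-week rate under Sample size.
- w = share of the intervention arm withdrawn. *Assumed* 5–10%.
- h = share of those withdrawn who would have healed. *Assumed* 30–40%.
- No such withdrawals among controls. *Assumed*, for simplicity.

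Formulas for the bias in the intervention proportion:
- Withdrawn patients dropped: (P − w·h)/(1 − w) − P
- Withdrawn patients counted as not healed: (P − w·h) − P = −w·h

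| w | h | Dropped | Counted as not healed |
|---|---|---|---|
| 5% | 40% | 0.480/0.95 = 50.5%, bias +0.5 points | −2.0 points |
| 5% | 30% | 0.485/0.95 = 51.1%, bias +1.1 points | −1.5 points |
| 10% | 40% | 0.460/0.90 = 51.1%, bias +1.1 points | −4.0 points |
| 10% | 30% | 0.470/0.90 = 52.2%, bias +2.2 points | −3.0 points |

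**Step 4: how far this depends on h.** If withdrawn patients heal like everyone else (h = 50%), dropping them gives no bias, while counting them as not healed gives −2.5 to −5.0 points. If none would heal (h = 0), dropping them gives +2.6 points (w = 5%) or +5.6 points (w = 10%), while counting them as not healed gives none. The sign depends on the handling rule, and the size on rates that the documents do not give.

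**Step 5: effect on the test.** With 112 randomised per arm, a two-sided 5% z test and withdrawn patients dropped, the type I error is 0.053 for w = 5%, h = 30%, and 0.062 for w = 10%, h = 30%. It reaches 0.127 only at w = 10%, h = 0.

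**Step 6: with continued follow-up.** If every withdrawn patient is followed and analysed as randomised, the bias from this source is zero, whatever w and h are.

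**The case against.** A reader might infer four stronger points, and the documents support none of them.

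- *That the rule contradicts ITT or makes it impossible.* An ITT set can still be formed by imputing these patients, counting them as not healed or censoring them. The choice is commonly left to an analysis plan, which is not shown. What stands is that any of these puts an assumption in place of data that could have been collected.
- *That the bias always favours the intervention.* It does so only if the patients are dropped, or censored as if non-informative, and would have healed less often than the rest. Counted as not healed, the same patients bias the result against the intervention, and by more in the illustration.
- *That the loss is confined to the intervention arm.* Only the fall example is tied to the programme; the general and inflammation criteria can apply to controls.
- *That the rule hides harm.* Causes of dropout are to be recorded, so injuries that trigger the rule are documented. The listed outcomes do not, however, include falls or injuries by arm.

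It can also fairly be said that the illustrated bias is small beside the 20-point target difference and a standard error of about √(2 × 0.25/112) = 6.7 points. Withdrawals of 5–10% (112 × 0.05 = 5.6 to 112 × 0.10 = 11.2 patients) also fit within the margin of 19. Both points stand. That margin protects numbers, though, not comparability: it does nothing about loss that differs by arm and by prognosis.

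Finally, follow-up may not be free. The protocol excludes people who cannot travel to the health centre, and an injured patient may become one.

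**Conclusion.** The point holds as a defect in a rule the article states outright. Mandatory exit from the study creates avoidable loss of the primary outcome, probably concentrated in the intervention arm, and so weakens the ITT analysis that the protocol promises.

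Size and direction cannot be taken from the documents. On the stated assumptions (5–10% withdrawn in the intervention arm only, 30–40% of them otherwise healing, 50% healing in both arms), the bias runs from about +0.5 to +2.2 points if they are dropped and from about −1.5 to −4 points if they are counted as not healed. That is modest, but it is avoidable at little cost, and outcomes not collected at the time may not be recoverable later. The wording finding is firm; the direction of bias is not.

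**What to change.** Separate stopping the programme from leaving follow-up:

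1. Leave the criteria for stopping exercise exactly as they are. This point takes no view on them.
2. Replace the requirement to leave the study with wording that these patients remain in follow-up, and that wound status and the 3- and 6-month outcomes are still collected, at wound-care visits or from the electronic record. Follow-up ends early only on withdrawal of consent, loss of contact or death.
3. State that they are analysed in their randomised arm, and report falls and injuries by arm.
4. Reconcile Setting and study population, Data collection methods, Losses in participation and Analysis on whether outcomes are collected after a withdrawal criterion is met.

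The cost is mainly wording. Participants are already under nursing wound care, and electronic records are already a named data source. The downside is some extra effort for the few patients who become unable to attend.

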### Randomization and masking

Simple random allocation to one of the two study groups via the Electronic Data Collection Notebook.

It is not possible to mask the intervention in this type of trial, although the analysis will be performed by professionals who are unaware of the allocation.

### Sample size

Previous studies have obtained 50% complete healing rates at 12 weeks follow-up. Sample size has been calculated considering a relevant post-intervention average difference of 20% of complete healing between the intervention and control groups. Assuming an alpha error of 0.05 and a beta error of 0.02, 93 patients are necessary for each group. Expecting a 20% loss to follow-up after a 3-month period, the required sample size is 224 patients (112 per group).

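### The stated beta error of 0.02 (98% power) does not fit 93 patients per group, which gives 80% power (beta 0.20)

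*Protocol article*

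**What the plan says.** The whole calculation is in one paragraph, under Sample size in the protocol article.

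- Reference rate: "Previous studies have obtained 50% complete healing rates at 12 weeks follow-up".
- Effect to detect: "a relevant post-intervention average difference of 20% of complete healing between the intervention and control groups".
- Error rates and result: "Assuming an alpha error of 0.05 and a beta error of 0.02, 93 patients are necessary for each group".
- Allowance for losses: "Expecting a 20% loss to follow-up after a 3-month period", which takes the total to 224, or 112 per group.

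The paragraph does not say whether alpha is one- or two-sided, or which arm the 50% belongs to. Power and beta appear nowhere else in the article. The Outcomes section makes complete healing at 3 months (yes/no) the primary outcome, together with time to healing, so the calculation addresses the binary part.

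**The concern.** A beta of 0.02 means 98% power, which is unusually high, and 93 per group is a small number for it with rates near 50% and a 20-point difference. Either the beta or the sample size is wrong.

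Beta is the design's stated chance of missing the benefit it calls relevant. As printed, a reader of a non-significant result is told that a true 20-point benefit would have been missed only 2 times in 100. If the true figure is about 20 in 100, the trial is credited with a sensitivity it does not have. The Discussion makes transfer into practice and the later cost-effectiveness work depend on whether the intervention is shown to be effective, so overconfidence in a negative result has a practical cost.

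**Working it through.** **Inputs, all from the Sample size section**

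- p1 = 0.50, taken as the control rate (assumption: the arm is not named)
- p2 = 0.70, from an absolute difference of 0.20 (0.50 against 0.30 gives the same n)
- alpha = 0.05, taken as two-sided (assumption), so z = 1.960
- beta = 0.02 as printed, so z = 2.054; for comparison beta = 0.20, so z = 0.842
- allocation 1:1

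**Formula (pooled variance under the null)**

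n per group = [z_alpha × √(2 p̄(1 − p̄)) + z_beta × √(p1(1 − p1) + p2(1 − p2))]² / (p2 − p1)²

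With p̄ = 0.60:

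- √(2 × 0.60 × 0.40) = √0.48 = 0.6928
- √(0.25 + 0.21) = √0.46 = 0.6782
- (p2 − p1)² = 0.04

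**Step 1: reproduce the 93.** At beta 0.20: (1.960 × 0.6928 + 0.842 × 0.6782)² / 0.04 = 92.999, rounded up to **93**. This is the protocol's figure exactly.

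**Step 2: use the printed beta.** At beta 0.02: (1.960 × 0.6928 + 2.054 × 0.6782)² / 0.04 = 189.2, rounded up to **190**. That is 380 evaluable patients in total, against 2 × 93 = 186.

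**Step 3: power at 93 per group.** z = (0.20 × √93 − 1.960 × 0.6928) / 0.6782 = 0.842, so power is **80.0%** and beta is 0.20. Exact enumeration of the chi-square test gives 79.9%.

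**Step 4: try to rescue 0.02 with other readings.** Patients per group needed at beta 0.02:

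| Reading | Two-sided | One-sided |
|---|---|---|
| 50% vs 70%, pooled | 190 | 161 |
| 50% vs 70%, unpooled | 186 | 158 |
| 50% vs 70%, continuity-corrected | 200 | 171 |
| 50% vs 70%, arcsine | 191 | 162 |
| 40% vs 60%, pooled | 198 | 168 |
| 50% vs 60% (20% read as relative), pooled | 794 | 674 |

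The smallest is 158, still far above 93.

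**Step 5: power at the sample sizes the plan implies (50% vs 70%, pooled)**

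| Patients per group | Two-sided | One-sided |
|---|---|---|
| 93 (as calculated) | 80.0% | 87.8% |
| 112 (all enrolled, no losses) | 86.8% | 92.5% |
| 89.6 (112 less 20%) | 78.5% | 86.7% |

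None reaches 98%. At 93 per group, 98% power (two-sided) needs a difference of about 27.7 points (50% against 77.7%).

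**The case against.** The best defence is that this is a misprint with no effect on the trial. The exact match at beta 0.20 makes it very likely that the calculation was done correctly and 0.2 was set as 0.02. Sample size, outcome, analysis and conduct would then be unaffected. The Analysis section also promises a point estimate and 95% confidence interval for the healing comparison, and that interval, not the planned beta, will show whether a 20-point benefit is excluded.

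Most of this stands. A misprint is the likeliest cause, and the error cannot alter the confidence interval. It does not make the printed figure harmless, because the article misstates the power of its primary comparison and a reader must redo the calculation to see which number is wrong.

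Three cautions also stand:

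- Two-sided testing and 50% against 70% are inferred because they reproduce 93; the article does not state them.
- The 80.0% is the power at 93 evaluable per group. The plan's own 20% loss leaves slightly fewer, and an intention-to-treat analysis of all 112 has somewhat more power.
- The figure covers the binary comparison only. Power of the log-rank test for time to healing was not computed.

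**Conclusion.** The concern holds. The stated beta and the stated 93 per group are incompatible under every reading tried. With 50% against 70% and two-sided alpha 0.05, 93 per group gives 80.0% power, so the true type II error is 0.20 and the article prints a tenth of it. Across the plan's own range, from 20% losses to none, two-sided power runs from 78.5% to 86.8%. The incompatibility does not rest on the assumed sidedness or on the arm given the 50% rate; the exact 80.0% does. The printed beta is most likely a slip for 0.2, but only the sponsor can confirm that.

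**What to change.** Ask the sponsor to confirm three inputs: the intended beta, the sidedness of alpha, and the arm with the 50% rate. If they are as inferred, restate the paragraph as: alpha 0.05 two-sided, beta 0.20 (80% power), 50% versus 70% complete healing at 3 months, 93 evaluable patients per group. Keep the sample size, and correct the beta wherever else it has been repeated.

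The cost is one corrected figure and two clarifications. The stated power becomes less favourable, but no patients are added and the analysis does not change.

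If 98% power was truly intended, the sample size is the error: 190 evaluable per group would be needed, or 190 / 0.8 = 237.5, rounded up to 238 per group (476 in total), to allow for 20% losses, against the 224 planned.

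### Minor: the 224 patients stated as required for 20% loss leave about 90 per group, not the 93 that the protocol says are necessary

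*Protocol article*

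**What the plan says.** All the relevant figures are in the Sample size section of the protocol article. The starting point is a healing rate from earlier work: "Previous studies have obtained 50% complete healing rates at 12 weeks follow-up". The target is "a relevant post-intervention average difference of 20% of complete healing between the intervention and control groups". The error rates and the resulting number follow: "Assuming an alpha error of 0.05 and a beta error of 0.02, 93 patients are necessary for each group". The last step is the loss allowance: "Expecting a 20% loss to follow-up after a 3-month period, the required sample size is 224 patients (112 per group". The formula for that step is not printed. The Methods part of the Abstract repeats the enrolment total of 224 and its split: "will be sequentially included (112 per group".

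**The concern.** The section states three things in sequence: 93 per group are needed, 20% will be lost, and 112 per group are therefore required. The third should follow from the first two, and it does not, because 112 reduced by a fifth is below 93. An allowance for loss exists to deliver the required number after the loss has happened, and at the protocol's own expected rate this one falls short.

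What is at stake is mainly the accuracy of the justification. Readers will check it, and a results paper will probably repeat it. The effect on the trial's ability to detect the target difference is small.

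**Working it through.** **Inputs, all from the Sample size section.** Control healing 50%; difference 20%, read as percentage points (50% versus 70%); alpha 0.05, sidedness not stated; beta printed as 0.02; 93 needed per group; 20% loss by 3 months; 112 per group enrolled, 224 in total.

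**Step 1: reproduce 93.** Two proportions, normal approximation with pooled variance under the null and no continuity correction:

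n = [z(α/2) × √(2p̄(1 − p̄)) + z(β) × √(p₁(1 − p₁) + p₂(1 − p₂))]² / (p₁ − p₂)²

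With p₁ = 0.50, p₂ = 0.70 and p̄ = 0.60, the two square roots are √0.48 = 0.6928 and √0.46 = 0.6782.

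- Two-sided alpha 0.05 and beta 0.20: (1.960 × 0.6928 + 0.8416 × 0.6782)² / 0.04 = 92.999, rounded up to **93**. This matches the protocol.
- Two-sided alpha 0.05 and the printed beta 0.02: **190** per group. One-sided with beta 0.02: 161. Neither matches.

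So 93 corresponds to beta 0.20. This is an inference from the number; the protocol does not say it.

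**Step 2: reproduce 112.** 93 × 1.20 = 111.6, rounded up to **112**, and 2 × 112 = **224**. Both match the protocol.

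**Step 3: apply the expected loss to 112.** 112 × 0.80 = **89.6**, so 89 or 90 per group remain against 93. In total, 224 × 0.80 = 179.2 against 2 × 93 = 186.

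**Step 4: number needed to retain 93.** 93 / (1 − 0.20) = 116.25, rounded up to **117** per group, **234** in total. Check: 117 × 0.80 = 93.6. The gap from the stated figure is 5 per group, or 10 in total, which is more than rounding.

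**Step 5: loss that 112 covers.** 1 − 93/112 = 0.1696, about **17.0%** (19 of 112 patients).

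**Step 6: effect on power.** Under the step 1 assumptions with beta 0.20, and for a comparison of proportions that leaves out every lost patient:

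| Evaluable per group | Power |
|---|---|
| 93 | 80.0% |
| 90 | 78.7% |
| 89.6 | 78.5% |
| 89 | 78.2% |

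The difference between 93 and 89.6 is about 1.5 percentage points.

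**The case against.** The strongest reply is that this hardly matters. The shortfall is 3 to 4 evaluable patients per group. The healing rate, the difference and the loss rate are all assumptions and could each be wrong by more than this. Allocation is by simple randomisation, so with 224 patients the standard deviation of one arm's size is about √224 / 2 = 7.5, larger than the 5 per group in dispute. All of that stands, and it is why the point is minor. It does not make the sentence correct.

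A second reply is that lost patients are not wholly lost. The Analysis section specifies intention to treat, with Kaplan-Meier curves, a log-rank test and Cox regression for time to healing, and data are collected every 14 days in the first 3 months. Someone who leaves early can contribute censored follow-up. This stands for the time-to-healing analysis, so the power figures in step 6 should not be carried over to it. It does not remove the point. Healing at 3 months as a yes/no outcome is also primary, and it is not observed in someone lost earlier. The Sample size section itself treats loss as reducing the usable number.

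A third reply is that the protocol shows no formula, so no one can say that the allowance was multiplied on. That is right: multiplication fits the printed figure exactly but is inferred. The shortfall does not depend on it, because 112 less 20% is below 93 however 112 was reached.

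A reader might go further and infer that the trial falls below a planned power of 80%. The document does not support that as stated. It prints "a beta error of 0.02", which means 98% power, and 80% appears only as the value that reproduces 93. The mismatch between the printed beta and 93 is a separate error. What the text supports directly is the shortfall against 93.

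**Conclusion.** Wrong as written, and minor. On the protocol's own figures, 112 per group does not leave 93 after the 20% loss it expects; it leaves about 90. It covers a loss of about 17%. Holding both the 93 and the 20% would take 117 per group, 234 in total, which is 10 more than stated. No other section repairs this, and the Abstract repeats the total.

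The shortfall rests only on printed numbers. The fall in power from 80.0% to about 78.5% rests on assumptions: 50% versus 70% healing, two-sided alpha 0.05, beta 0.20 in place of the printed 0.02, and a two-proportion comparison without the lost patients. A reader might take the finding as evidence of a seriously underpowered trial. A loss of about 1.5 points under those assumptions does not support that.

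**What to change.** Keep 224 and restate what it provides. In the Sample size section, say that 112 per group retains the required 93 only if loss by 3 months is at most about 17%, and that at the expected 20% loss about 90 per group remain. The Abstract figure can then stay as it is.

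If power is quoted, give its assumptions in the same sentence: 50% versus 70% healing, two-sided alpha 0.05, beta 0.20, and a two-proportion comparison excluding lost patients, with about 79% power at 20% loss instead of 80%. The printed beta of 0.02 must be corrected there too, once the sponsor has confirmed that 0.20 was intended. Otherwise an 80% power statement would stand beside a beta that implies 98%.

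If the sponsor prefers to keep both 93 per group and the 20% allowance, the total becomes 234 in the Sample size section and the Abstract, at the cost of 10 more patients. Restating at 224 costs wording only; its one downside is a stated power about 1.5 points less favourable.
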